**Fig. 1 Fig1:**
[figure not shown]
The study flow chart. Note: for patients who relapse during follow up, the study treatments will be stopped and patients will be referred to appropriate alternative treatments and follow up will be continued for cost data collection. RA: Rheumatoid Arthritis; csDMARDs: conventional synthetic disease-modifying anti-rheumatic drugs; MTX: methotrexate; HCQ: hydroxychloroquine; SSZ: sulfasalazine; TNFi: Tumor necrosis factor α inhibitors; CR:clinical remission; LDA: low disease activity

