### Follow up schedule and data collection

A total of at most 14 visits will be scheduled. Data to be collected at each visit are summarized in Table 1.

**Table 1 Tab1:** Follow up schedule and data to be collected

Study period	Induction treatment stage		Randomized stage										Early exit
Visit	S1	S2-4	V0	V1	V2	V3	V4	V5	V6	V7	V8	V9	
	Wk0	Wk 4\8\12	Wk0	Wk4	Wk8	Wk12	Wk20	Wk28	Wk36	Wk44	Wk52	Wk60	
ICF	√												
Demographic data	√												
Past history and medication history collection	√												
Physical examination	√	√ √	√	√	√	√	√	√	√	√	√	√	√
Urine βHCG (if applicable)	√												
BCC, renal function, liver function, ESR,CRP,RF	√	√	√	√	√	√	√	√	√	√	√	√	√
Assessment committee examination	√	√ √	√	√	√	√	√	√	√	√	√	√	√
IC/EC judgement	√												
Randomization		√											
Hand X-ray-ran	√		√									√	√
Ultrasound of double hands	√		√									√	√
Anti-CCP antibody	√											√	√
Cost of exam and treatment	√		√	√	√	√	√	√	√	√	√	√	√
HAQ-DI/EQ-5D	√		√			√						√	√
Study Medication record	√	√	√	√	√	√	√	√	√	√	√	√	√
Concomitant medication record	√	√ √	√	√	√	√	√	√	√	√	√	√	√
AE record	√	√ √	√	√	√	√	√	√	√	√	√	√	√

*ICF* informed consent form, *BCC* blood cells count, *ESR* erythrocyte sedimentation rate, *CRP* c reactive protein, *RF* rheumatoid factor, *IC/EC* inclusion criteria/exclusion criteria, *Anti-CCP antibody* anti-cyclocitrulline polypeptide antibody, *HAQ-DI/EQ-5D* Health Assessment Questionnaire Disability Index/ Euro Qol five dimensions questionnaire, *AE* adverse event

Patients will be requested to return the residual drugs to obtain new drugs at each visit. Laboratory tests must be performed in the eligible study centers. These strategies were designed to improve adherence of subjects.

Subjects who relapse or cannot tolerant adverse effects before the end of the trial should exit the trial and receive empirical treatment, including but not limited to, other biological agents, or csDMARDs combination therapy. All patients who exit early will be kept in following up for the safety and cost-effectiveness analysis.

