Pharmaceutical economics analysis will be performed. Base case analysis and sensitivity analysis will be performed by decision tree model based on Per-Protocol Set (Fig. 2). A series of one-way deterministic sensitivity analysis will be conducted. For the cost-effectiveness analysis, the proportion of not relapse will be taken as effectiveness. The direct cost (medical expenses), indirect cost (productivity lost), total cost (the total of direct and indirect cost), and average cost/effectiveness ratio of each treatment strategy will be calculated. Direct cost will include the cost of experimental drugs, laboratory and radiology examinations, AE/SAE treatment, traffic expenses and accommodation fees directly related with follow-up visit. Indirect cost will include loss of income due to the patients’ and their family’s inability to work due to RA. The incremental cost effectiveness ratio (ICER) of group A and group B against group C will be calculated. Cost-utility analysis will be performed by using EQ-5D-5L and SF-6D as utility index. The costs and average cost/utility ratio of each treatment strategy will be calculated. The incremental cost utility ratio [the cost of increase 1 quality adjusted life year (QALY)] of group A and group B against group C will be calculated. The treatment strategy will be considered to have cost-utility if the incremental cost utility ratio is below 3 times of China’s per capita GDP in the past year (¥100,000).

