Once approved, the study protocol may not be changed at will. In case the protocol must be verified, the principle investigator, the responsible person of clinical research center and the principle investigators at all sites should discuss and agree on the updates. When an agreement is achieved, protocol revision note should be formulated and signed, and the revised protocol should be submitted to the IRB for approval before implementation.

To guarantee the quality of the study, all the staffs should receive a standard training before start of the trial, including good clinical practice (GCP), subject protection and ethical requirements, study protocol, standard operation procedures, CRF filling instructions, and standard assessment method of disease activity. The project training will run throughout the whole process of the study. The investigators and the study coordinators can add training contents according to actual need.

Treatment that changes during the whole study period will be recorded. To guarantee the correct injection method, each injection of TNFi will be performed in the study centers by medical staffs rather than at home by patients themselves.

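### The direct-cost list has no item for treatment after relapse or early exit, although patients stay in follow-up for cost data; applied as written, it biases the cost-effectiveness ratios

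*Protocol article*

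**What the plan says.** The Statistical analysis section of the protocol article sets the cost items: "Direct cost will include the cost of experimental drugs, laboratory and radiology examinations, AE/SAE treatment, traffic expenses and accommodation fees", where the last items read in full "traffic expenses and accommodation fees directly related with follow-up visit". Indirect cost is separate: "Indirect cost will include loss of income due to the patients’ and their family’s inability to work due to RA". For effectiveness, "the proportion of not relapse will be taken as effectiveness". ICERs and cost-utility ratios are planned for A and for B, each against C.

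Under Follow up schedule and data collection, patients who relapse or cannot tolerate treatment "should exit the trial and receive empirical treatment, including but not limited to, other biological agents, or csDMARDs combination therapy". The same paragraph keeps early exits in follow-up for the safety and cost-effectiveness analysis. The note to Fig. 1 says that study treatments stop at relapse and that "follow up will be continued for cost data collection". Table 1 has a row for the cost of examinations and treatment, ticked at every randomised-stage visit and at early exit.

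**The concern.** The only RA drugs in the list are the experimental drugs. Treatment started after relapse is outside the study regimen, so it has no clear place there. It is not clearly AE/SAE treatment either: the follow-up section and the Exit criteria both name relapse separately from adverse effects, and relapse is the efficacy endpoint. The plan thus follows patients for costs that its own definition does not take in.

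On the listed items, a relapse ends study-drug cost and puts nothing in its place. The saving from avoiding relapse, a main economic argument for the triple therapy against MTX alone, then drops out of the numerator while the relapse itself stays in the denominator. Cost-effectiveness is in the title and the stated aim, and cost per relapse avoided is the first secondary outcome listed.

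**Working it through.** **Inputs.** From Sample size estimation: relapse rate pA = 0.50 and pC = 0.74, 80 patients per arm. For B the article says only that the rate may be similar to A, so I take pB from 0.20 to 0.50 as an assumption. The article gives no unit costs. Let R be the mean cost of treatment from relapse to week 60 per relapsing patient; every value of R below is an assumption.

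**The plan's own figure.** No ICER is stated. The relapse rates come from the sample size, which reproduces with the unpooled normal formula: (1.960 + 0.842)² × (0.50×0.50 + 0.74×0.26) / 0.24² = 7.849 × 0.4424 / 0.0576 = 60.3, so 61 per group, as stated. This point does not dispute it.

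**Patients affected.** 80 × 0.50 = 40 in A and 80 × 0.74 = 59 in C.

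**A versus C, equal R.** The change in incremental cost when the omitted cost is restored is pA·R − pC·R = (0.50 − 0.74)R = −0.24R. Relapses avoided per patient are 0.74 − 0.50 = 0.24. The ICER changes by −0.24R / 0.24 = −R. The list as written therefore overstates the ICER by R per relapse avoided.

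| Assumed R (yuan) | Incremental cost overstated | ICER overstated |
|---|---|---|
| 5,000 | 1,200 | 5,000 |
| 20,000 | 4,800 | 20,000 |
| 50,000 | 12,000 | 50,000 |

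**B versus C, equal R.** The change in incremental cost is (pB − 0.74)R: −0.54R, −0.39R and −0.24R at pB = 0.20, 0.35 and 0.50. Dividing by 0.74 − pB gives −R each time, for any pB below 0.74.

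**A versus C, unequal R.** The ICER change is (0.50·R_A − 0.74·R_C) / 0.24. It is zero at R_A / R_C = 0.74 / 0.50 = 1.48.
- R_A = 10,000, R_C = 20,000: (5,000 − 14,800) / 0.24 = −40,833.
- R_A = 30,000, R_C = 20,000: (15,000 − 14,800) / 0.24 = +833.

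Equality of R cannot be taken for granted. A patient in A relapses on a csDMARD combination (or before TNFi stops) and one in C on MTX alone (or likewise), so what follows may differ in kind and length.

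**A versus B.** No ratio is listed and the comparison is exploratory, but it is part of the stated aim. The omitted difference is (0.50 − pB)R: zero if the rates are equal, up to 0.30R in A's favour at pB = 0.20.

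**The case against.** The wording may be illustrative: a list of what will be included need not be complete, and a condensed article may leave costing rules to the full protocol. The cost follow-up suggests that the investigators mean to use these costs. The decision tree (Fig. 2) is not shown, so its relapse branches may carry them. The SAE definition under Study outcomes covers conditions that lead to stopping study drugs, so treatment of relapse might be read as SAE treatment. Treatment after relapse may also be csDMARDs rather than a biologic, which would make R small.

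Much of this stands. It means that the omission is an unreconciled definition, not proof that the costs will be dropped, and that the size depends on R. It does not remove the conflict: the article chose to itemise direct cost, restricted drug cost to experimental drugs, and elsewhere treats relapse and adverse effects as separate reasons for exit. If relapse was meant to enter as an SAE, the text has to say so.

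A reader might also infer that relapse counts as an overall saving. That goes too far. Income loss due to RA remains in total cost, and after week 12 patients in A and C take only csDMARDs, which the Background calls much cheaper than biologics, so stopping them saves little.

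**Conclusion.** The definition of direct cost and the plan for cost follow-up have to be reconciled. If the list is applied as written, treatment cost is left out for about half of A and three quarters of C at the planned rates. With equal R, the A versus C and B versus C ICERs are each overstated by R per relapse avoided, which favours C; the B result needs B to relapse less than C. With R_A above about 1.48 × R_C, the A versus C bias goes the other way, so it cannot be called conservative. Cost-utility ratios use the same costs and are exposed too, by an amount that depends on QALY differences the article does not give. The primary relapse comparison is unaffected.

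One stronger reading is not supported. Because "each injection of TNFi will be performed in the study centers by medical staffs rather than at home by patients themselves", a reader might infer that injection trips and lost work time are charged to B and distort every ICER. Travel cost is limited to follow-up visits, and indirect cost to inability to work due to RA. A and C both have TNFi for 12 weeks, so such trips would cancel between them for patients who stay on schedule. Weekly dosing is stated only for induction. At most, the text could say that attendance only for an injection is not a follow-up visit.

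**What to change.** In the Statistical analysis section, define direct cost as all RA-related drug and care costs from randomisation to week 60 in every arm, including treatment after relapse or early exit, and make the relapse branches of the decision tree carry them. For clarity, add that attendance only for a centre injection does not count as a follow-up visit for costing.

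The change costs a few lines of text, best settled before database lock, and some extra costing work. Follow-up for these costs is already planned, so no new visits are needed.

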## Abstract

**Background:**

Tumor necrosis factor α inhibitors (TNFi) is effective for rheumatoid arthritis (RA) patients who fail to conventional synthetic disease-modifying anti-rheumatic drugs (csDMARDs). Because of high cost, the discontinuation is common but often lead to disease relapse. The study aims to investigate, if the combination therapy of csDMARDs is more effective in reducing disease relapse than methotrexate (MTX) monotherapy, and more cost-effective than continuing TNFi and MTX.

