An increasing number of studies showed that the efficacy of csDMARDs combination therapy is superior to monotherapy [9]. The classical combination strategy of MTX plus hydroxychloroquine (HCQ) and sulafasalazine (SSZ) provided good response and safety [10, 11]. It has been reported that 77% refractory RA patients had 50 percent improvement at nine months without major drug toxicity with MTX + HCQ + SSZ triple therapy [10]. Nevertheless, the BeSt study showed that there was little difference between csDMARD monotherapy and combination therapy [12]. A previous study showed that combination therapy of MTX and cyclosporin could not prevent relapse in 58% RA patients after discontinued biological DMARD [4]. In that study, cyclosporin was just initiated at the discontinuation of TNFi. However, considering the delayed efficacy of csDMARDs, it is preferable to overlap csDMARDs and TNFi for several weeks before discontinuation of TNFi.

Long-term therapy of bDMARDs poses a heavy burden on RA patients and the society. The commonly used csDMARDs are much cheaper than biologics [13]. An investigation showed that only 9% of Chinese RA patients received biological DMARDs. However, the cost of biologics accounted for 49% of the total cost for RA treatment medications. Due to lack of high quality research, it is still under debate whether the benefit is worth such high cost.

This 1:1:1 randomized enrollment parallel group study aims to investigate, among RA patients who are refractory to csDMARDs but have achieved CR or LDA after treatment with TNFi and MTX, if the triple therapy of MTX + HCQ + SSZ is more effective in reducing the relapse rate than MTX monotherapy, and more cost-effective than continuing the treatment of TNFi and MTX.

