### Study outcomes

The primary outcome will be disease relapse, which is defined as DAS28-CRP increases by at least 0.6 compared with that at randomization and is greater than 3.2 simultaneously.

The secondary outcomes will include the following: the incremental cost per reducing 1 case of relapse; change of disease activity score from baseline, assessed by DAS28-CRP, DAS28-ESR, CDAI and SDAI, at 60 weeks after randomization; duration of maintaining CR or LDA after randomization; change of hands X ray modified Sharp score at 60 weeks after randomization; ultrasound remission of hands at 60 weeks after randomization; Health Assessment Questionnaire Disability Index (HAQ-DI) and health related quality of life [the five-levele EuroQol-5D-5L (EQ-5D-5L) and short form-6D (SF-6D)] at 60 weeks after randomization; adverse events and complications; and patient reported outcomes (PRO) including rash, nausea, vomiting, diarrhea, abdominal pain and fever.

All outcomes will be measured after 60 weeks.

Responsible physicians will monitor and record any adverse events (AEs) during the whole trial. Expected AEs will include: allergy; ALT and AST elevation; hemocytopenia; infection; digestive tract symptom including nausea and vomiting; and hemorrhage of digestive tract defined by fecal occult blood positive, etc. In case of AEs, symptomatic treatment or reduction of drug dosage or even discontinuation of drugs will be carried out when necessary. If the drugs is tapered or discontinued, a serious AE will be considered and the patient should exit the study. Physicians will assess the association between intervention and AEs on a 6-point scale (1 = definitely related; 2 = probably related; 3 = possibly related; 4 = probably not related; 5 = definitely not related; 6 = unknown). All AEs will be categorized into three levels using the Spilker classification [(1) mild = not need additional intervention, nor significantly inhibit normal life function of the participant; (2) moderate = significantly inhibit the normal life function of the participant, and may need additional intervention, recovering afterwards; and (3) severe = require intensive intervention, and leave sequelae).

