#### Sample size estimation

According to the study purposes, a superiority design was considered appropriate. Our hypothesis is that the relapse rate in group A (triple therapy group) will be lower than that in group C (MTX monotherapy group) in 60 weeks after randomization.

Sample size was calculated by PASS 11.0. It was reported that for patients with established RA achieving CR or LDA by TNFi combined with MTX, 24% to 85% suffered from disease relapse after discontinuation of TNFi [4–7]. When combined csDMARDs preserved after TNFi removed, the rate of relapse was 51.2–58% [4, 7]. We assume that adding HCQ + SSZ 3 months before the removal of TNFi may somehow decrease the relapse. Accordingly, we expect the relapse rate as 50% in patients in triple therapy group, and 74% in MTX monotherapy group. With a power of 0.8 and a significance level of 0.05 (two-sides), using a 1:1:1 treatment allocation of enrollment, to detect the difference of relapse rate between the two groups, the required sample size is 61 for each group. Given the estimated dropout rate of 20%, we intend to recruit a total of 240 subjects (80 for each group).

We assume that the relapse rate may be similar between group A and group B (TNFi maintenance therapy group), and the cost-effectiveness may be better in group A than in group B. The relapse rate and cost-effective comparison between group A and group B will be exploratory and there was no relevant research hypothesis, so the sample size was not calculated by it.

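### The economic aim compares triple therapy (A) with continued TNFi + MTX (B), but every incremental ratio and the acceptance rule are defined only against MTX monotherapy (C)

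*Protocol article*

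**What the plan says.** All references are to the protocol article.

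- **Aim.** The abstract's Background asks whether combination therapy beats MTX monotherapy on relapse "and more cost-effective than continuing TNFi and MTX". The last paragraph of the main Background repeats it: triple therapy is to be "more cost-effective than continuing the treatment of TNFi and MTX". The Discussion also names TNFi maintenance as a comparator.
- **Expectation.** Sample size estimation supposes similar relapse in A and B, and that "the cost-effectiveness may be better in group A than in group B". It calls the A-B comparison of relapse and cost-effectiveness exploratory, without a hypothesis and not used for sizing.
- **Outcome.** Study outcomes lists "the incremental cost per reducing 1 case of relapse" as a secondary outcome and names no comparator.
- **Analysis.** Statistical analysis fixes the contrasts: "The incremental cost effectiveness ratio (ICER) of group A and group B against group C will be calculated". The incremental cost-utility ratio follows the same pattern: "the cost of increase 1 quality adjusted life year (QALY)] of group A and group B against group C will be calculated". For each arm alone, costs and the "average cost/effectiveness ratio of each treatment strategy will be calculated".
- **Decision rule.** A strategy is accepted if its incremental cost-utility ratio falls below three times China's "per capita GDP in the past year (¥100,000").
- **Uncertainty.** A bootstrap interval for the ICER and an acceptability curve are planned, with no contrast named.

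**The concern.** The aim is a choice between A and B. The planned incremental ratios, and the only stated acceptance rule, set each of them against C. A ratio against C says whether a strategy is worth paying for when the alternative is MTX alone. It does not say whether the extra cost of B over A buys enough extra benefit.

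This is more than condensed detail: the text names the comparator twice and attaches a decision rule to it. At stake is the economic conclusion, which is in the trial's title and aim. Both A and B could be reported as acceptable without the choice between them being put to any stated test. If the A-B measure is then chosen after the costs are known, it is no longer prespecified.

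**Working it through.** **1. What the rule uses.** Write K for mean cost, Q for mean QALYs and T for the threshold. B is accepted when

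(K_B − K_C) / (Q_B − Q_C) < T.

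Neither K_A nor Q_A appears. Suppose Q_A = Q_B > Q_C and K_A < K_B, so that A dominates B. B is still accepted whenever K_B − K_C < T × (Q_B − Q_C), and A is then accepted too, since it costs less for the same gain. The rule does not separate them.

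**2. Inputs for an illustration.** Sample size estimation expects relapse of 50% in A and 74% in C, so the proportions not relapsing are E_A = 0.50 and E_C = 0.26. (The stated 61 per group for this contrast reproduces: (1.96 + 0.8416)² × (0.50×0.50 + 0.74×0.26) / 0.24² = 60.28, rounded up. The point does not depend on it.) The article gives no costs and no E_B. Assumed here: E_B from 0.45 to 0.75, and costs for C / A / B of either 10,000 / 15,000 / 60,000 or 10,000 / 12,000 / 40,000.

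**3. Cost per relapse avoided, first cost set.** A vs C = 5,000 / 0.24 = 20,833 throughout. B vs C = 50,000 / (E_B − 0.26). B vs A = 45,000 / (E_B − 0.50).

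| E_B | B vs C (planned) | B vs A (the aim) | Multiple |
|---|---|---|---|
| 0.45 | 263,158 | B dominated | – |
| 0.50 | 208,333 | undefined; A cheaper, equal effect | – |
| 0.55 | 172,414 | 900,000 | 5.2 |
| 0.60 | 147,059 | 450,000 | 3.1 |
| 0.75 | 102,041 | 180,000 | 1.8 |

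The second cost set gives A vs C = 2,000 / 0.24 = 8,333. B vs C is 157,895, 125,000, 103,448, 88,235 and 61,224. B vs A is dominated, undefined, 560,000, 280,000 and 112,000 (multiples 5.4, 3.2 and 1.8). These are costs per relapse avoided, so the per-QALY threshold cannot be applied to them.

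**4. Average ratios.** In the first cost set they are 15,000 / 0.50 = 30,000 for A and 10,000 / 0.26 = 38,462 for C. For B they run from 60,000 / 0.45 = 133,333 to 60,000 / 0.75 = 80,000. A has the lowest average ratio, and a lower ratio against C than B has, in every row. Yet the B-versus-A answer moves from dominated to 180,000. Neither set of planned ratios answers the A-B question.

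**5. Precision of the two effect differences.**
- A vs C: expected difference 0.24. SE = √((0.25 + 0.1924)/80) = 0.074, or 0.083 at 64 per arm (80 less 20% dropout). The difference is 3.2 or 2.9 SEs from zero.
- A vs B, if both relapse at 50%: 95% half-width = 1.96 × √(2 × 0.25/80) = 0.155, or 0.173 at 64 per arm, around an expected difference of zero.

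A ratio interval is therefore workable for A vs C at the expected effect. An A-B ratio would have a denominator that is not separated from zero.

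**6. Threshold.** If ¥100,000 is already three times GDP per head, GDP per head is 100,000 / 3 = ¥33,333 and the threshold is ¥100,000. If ¥100,000 is GDP per head, the threshold is ¥300,000. The readings differ threefold. The study is scheduled from October 2015 to September 2022, and no reference year is given.

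**The case against.** The strongest reply is that the A-B comparison is planned: the sample size section calls it exploratory. Cost and effectiveness are also to be calculated for each arm, so B's extra cost over A and the effect difference are each one subtraction away. If A is cheaper and no worse, that will be visible without any ratio. The acceptability curve is not restricted to contrasts with C. The primary hypothesis, A versus C on relapse, is untouched.

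Much of this stands. A reader might infer that the A-B result will never be computed, or that the trial cannot support or refute its economic claim. The article does not support either reading: the comparison is mentioned and the arm-level outputs will exist. A reader might also infer that the planned bootstrap interval fails because A and B relapse alike. That does not follow for the planned A-versus-C ratio, whose expected denominator is about 3 SEs from zero. It is a reason for care only once an A-B measure is added.

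What the reply leaves standing is narrower. The exploratory comparison has no incremental measure, and the only acceptance rule is tied to a ratio against C. Exploratory status explains why the trial was not sized for A versus B. It does not explain prespecifying a different contrast from the one in the aim.

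**Conclusion.** The point holds as a mismatch between the stated economic aim (A versus B) and the defined incremental contrasts and decision rule (A and B, each against C). As written, the rule can accept B even when A is cheaper and no worse. That follows from the form of the rule and needs no assumed figures.

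How far B versus A departs from B versus C cannot be determined from the article. Under the assumptions shown, the result is B dominated, an undefined ratio, or a multiple between about 1.8 and 5.4. A single multiple from that range should not be quoted as the size of the problem, because it depends mainly on the assumed gap between A and B. The gap is in the plan and not in the data to be collected.

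The threefold threshold ambiguity is a separate, secondary point. It affects the same rule but has no bearing on which arms are compared.

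**What to change.** In the economic part of Statistical analysis:

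1. Add the direct A-versus-B incremental comparison, as cost per relapse avoided and cost per QALY. Alternatively, specify a full incremental analysis of all three arms, ranked by cost, with dominance and extended dominance. Apply the decision rule to that result.
2. Because A and B are expected to relapse similarly, report A versus B as the cost difference, the effect difference and the incremental net monetary benefit, T × (Q_A − Q_B) − (K_A − K_B), with a bootstrap interval. Draw the already planned acceptability curve for this contrast. Do not rely on an A-B ICER with an interval alone.
3. Keep A versus C and B versus C as supporting results.
4. Separately, state the threshold as one figure in yuan and give its reference year.

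The cost is a wording change and a little more analysis. No new data or patients are needed. The article describes the trial as ongoing, with 123 patients in the randomised stage, so the change is best made before the database is locked.

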#### Statistical analysis

All statistical analyses will be performed using SAS 9.2.

The compatibility of baseline data among three groups will be checked. Student’s t-test or Wilcoxon rank sum test will be used for quantitative variables. Chi-square test or Fisher’s exact test will be used for categorical variables. The Cochran–Mantel– Haenszel test or the Wilcoxon rank sum test will be used for ordinal variables.

To compare the relapse rate between triple therapy group and MTX monotherapy group, the intention-to-treat principle will be followed. Considering the influence of central effect, the collected data will be estimated by mantel Haenszel method with stratification by study centers. Kaplan–Meier curves will be used to show the differences of relapse rate among three groups. The disease activity changes and other continuous secondary outcomes (Sharp score, ultrasonic Doppler score and HAQ-DI score) will be compared between the study groups using the covariance analysis model. Per protocol analyses will also be conducted as sensitivity analyses.

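### The cost-utility analysis as described does not adjust for the EQ-5D value collected at randomisation, which gives up precision and lets chance baseline imbalance into the QALY difference

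*Protocol article*

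**What the plan says.** Table 1 of the Protocol article (Follow up schedule and data collection) puts HAQ-DI and EQ-5D in one row, collected at S1, V0, week 12, week 60 and early exit. Study outcomes lists HAQ-DI, EQ-5D-5L and SF-6D at week 60 as secondary outcomes.

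Statistical analysis assigns a covariance model to disease activity change and to "other continuous secondary outcomes (Sharp score, ultrasonic Doppler score and HAQ-DI score". EQ-5D-5L and SF-6D are not named there.

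The economic part of the same section plans a decision tree on the Per-Protocol Set. On utility it says: "Cost-utility analysis will be performed by using EQ-5D-5L and SF-6D as utility index". For each arm, "The costs and average cost/utility ratio of each treatment strategy will be calculated". The contrast between arms is "The incremental cost utility ratio [the cost of increase 1 quality adjusted life year (QALY)] of group A and group B against group C", judged against a threshold of three times per capita GDP. A non-parametric bootstrap is stated for the interval of the incremental cost-effectiveness ratio and for the acceptability curve, and the economic work is assigned to TreeAge. No baseline adjustment appears in any of these steps.

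Under Randomization, allocation is stratified by centre and gender only.

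**The concern.** A QALY measured from randomisation starts at the V0 utility, and later utilities are normally correlated with it. An arm that starts higher by chance will therefore tend to show more QALYs without any treatment effect. Nothing in the allocation balances V0 utility.

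The QALY difference is the denominator of the ratio that decides whether a strategy counts as having cost-utility. Cost-effectiveness is in the trial's title and aims, yet the sample size was set on relapse alone, so precision on the economic side is whatever the data give. The V0 value that would recover some of that precision is already on the collection schedule, and the neighbouring measure in the same table row is assigned a covariance model.

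**Working it through.** **Plan's own figure.** The article gives no utility SD, correlation, QALY difference or QALY interval, so nothing on this point can be reproduced. The only reproducible design figure is the relapse sample size, used here just for the number per arm. The inputs are "we expect the relapse rate as 50% in patients in triple therapy group, and 74% in MTX monotherapy group", with "With a power of 0.8 and a significance level of 0.05 (two-sides), using a 1:1:1 treatment allocation of enrollment". The unpooled formula gives (1.960 + 0.842)² × (0.50×0.50 + 0.74×0.26) / 0.24² = 60.28, rounded up to 61, which matches "the required sample size is 61 for each group". Allowing for 20% dropout, 61/0.8 = 76.25, so 77 are needed and the planned 80 is enough.

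**Assumptions (not in the article).** Each patient's QALY is the straight-line area through V0, week 12 and week 60. Utilities have the same SD at each visit and an equal correlation r between visits. I show r from 0.3 to 0.7, with 0.2 as a low case, and SD 0.10 to 0.20.

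**Weights in years.** V0: (12/2)/52 = 6/52. Week 12: ((12+48)/2)/52 = 30/52. Week 60: (48/2)/52 = 24/52. V0 carries 6/60 = 10% of the area directly; the rest of its influence comes through correlation.

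**Formulas, in units of the utility SD.**
- Slope of QALY on V0: b = 6/52 + r × 54/52.
- QALY variance: V = (1 − r) × 1512/2704 + r × 3600/2704, where 1512 = 6² + 30² + 24² and 3600 = 60².
- Correlation of V0 with QALY: b/√V.
- Adjusted to unadjusted interval width: √(1 − b²/V).
- If only week-60 utility is used, the width ratio is √(1 − r²).

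At r = 0.5: b = 0.115 + 0.519 = 0.635; V = 0.280 + 0.666 = 0.945; correlation 0.635/√0.945 = 0.65; variance cut 0.403/0.945 = 43%; width ratio √0.574 = 0.76.

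| r | slope b | correlation | variance cut | narrowing, area QALY | narrowing, week 60 only |
|---|---|---|---|---|---|
| 0.2 | 0.32 | 0.38 | 15% | 8% | 2% |
| 0.3 | 0.43 | 0.48 | 23% | 12% | 5% |
| 0.5 | 0.63 | 0.65 | 43% | 24% | 13% |
| 0.7 | 0.84 | 0.80 | 65% | 40% | 29% |

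**Absolute width.** With SD 0.20 and 61 per arm, the 95% half-width 1.96 × SD × √(2V/n) goes from 0.063 to 0.055 (r = 0.3), 0.069 to 0.052 (r = 0.5) and 0.074 to 0.044 (r = 0.7).

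**Carry-over of chance imbalance.** The standard error of the V0 difference is SD × √(2/n). At 80 per arm it is 0.016 for SD 0.10 and 0.032 for SD 0.20; at 61 per arm it is 0.018 and 0.036. A V0 difference of 0.03 is thus unremarkable at the higher SD. It moves the unadjusted QALY difference by b × 0.03: 0.013, 0.019 and 0.025 at r = 0.3, 0.5 and 0.7.

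**The case against.** The strongest reply is that this is a condensed article whose analysis plan is not shown, and adjustment for baseline utility is often settled there. That stands as far as it goes. A reader might infer that raw arm averages will be compared. The article never says raw or unadjusted; the sentence on average ratios defines a per-arm summary, and how the QALY difference is estimated is not stated. Still, the article sets out the economic steps one by one and names the outcomes that get a covariance model. An analysis plan that followed this text would not adjust. The bracketed list could be read as examples, which is a further reason to make it explicit.

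Other stronger readings also fail:
- A reader might call the planned result biased. Randomisation keeps the unadjusted difference unbiased on average; the shift is conditional on the imbalance that occurs. The Per-Protocol Set may add imbalance that is not due to chance, but that is a separate issue, and V0 adjustment does not fully cure it.
- A reader might say the stated bootstrap interval is too wide by the figures above. That interval is stated for the cost-effectiveness ratio, whose effect measure is freedom from relapse. No QALY interval, test or power is stated, so a power gain has no object here. Uncertainty in a cost-utility ratio also depends on costs.
- The three-point area is an assumed estimator. Half of group A and 74% of group C are expected to relapse and exit, so many patients will not supply all three points, and equal correlation out to week 60 is doubtful. All patients are at low disease activity at V0, which may restrict the spread of V0 utility. The tree figure is not shown, and if utilities attach to relapse and non-relapse branches, V0 imbalance enters differently.

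These points reduce the size and certainty of the gain. They do not remove it: adjusted utilities can feed a tree, and some gain remains at every correlation examined, though at r = 0.2 with week-60 utility alone it is only 2%.

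**Conclusion.** The point holds as a modest improvement in precision and in protection against chance imbalance. It is not a demonstrated error. What the article supports is that V0 EQ-5D is collected, that the cost-utility analysis as described makes no use of it for adjustment, and that the covariance list names HAQ-DI but not the utility collected at the same visits.

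The size is illustrative. It rests on an assumed equal correlation of 0.3 to 0.7 and, for the 12% to 40% narrowing, on a three-point area; the 5% to 29% figure applies if only week-60 utility is used. Neither range translates directly into the cost-utility ratio.

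**What to change.** In Statistical analysis, add week-60 EQ-5D-5L to the outcomes analysed by covariance, with its V0 value as covariate. In the economic part, estimate the QALY (utility) difference for A against C and for B against C by regression on arm and V0 EQ-5D utility. Use the adjusted values as the utility inputs of the decision tree and of the incremental cost-utility ratio. Wherever the bootstrap is applied to that ratio, refit the regression in each replicate. Treat SF-6D the same way if a V0 value is collected; Table 1 does not list SF-6D.

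The cost is a few lines of text and a small amount of analysis outside TreeAge. For EQ-5D no new data, visits or patients are needed. Trial status reports 123 patients randomised with the trial ongoing, so on that status the change could be settled before database lock.
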